**Fig 3 pone.0346508.g003:**
[figure not shown]
25m walking loop consisting of two straight and two curve sections.

Following Walks #2 and #4, a two-part washout (WO1 and WO2) will be implemented to minimise any potential carryover effects from the previous auditory cue. Part 1 (of WO1 and WO2) will involve participants sitting and counting backwards in their heads from 30 to 0 in increments of 1 to disengage any psychological responses triggered by the cueing modality [72]. Part 2 (of WO1 and WO2) will consist of a 1-minute walk at the participant’s natural pace, to further reset their gait but also to assess whether any carryover effect remains before the next cue begins. This approach ensures each cue’s effects are evaluated independently of preceding sequences:

Sequence 1–20 participants: NC, Me, WO1, IM, WO2, and VM.Sequence 2–20 participants: NC, IM, WO1, VM, WO2, and Me.Sequence 3–20 participants: NC, VM, WO1, Me, WO2, and IM.

Accordingly, the complete sequence consists of (Fig 4):

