A two-way mixed ANOVA will be used to assesses the effects of cueing modality and walk order on outcomes, i.e., cadence, gait speed, stride length, and CV_stride-time_. Comparable to the referenced PD study, cueing modality will be modelled as a within-subject factor, while walk order as a between-subject factor to account for potential sequence effects. For each outcome, within-participant changes from baseline will be calculated using cue-specific difference scores. To account for differences in scale and statistical distribution among the outcomes, change scores will be computed using Equations (30)-(31):

Percentage change of gait speed and stride length from baseline, calculated as:

$$\%\Delta =\frac{\text{Cue Value}-\text{Baseline Value}}{\text{Baseline Value}}\times \text{1}\text{0}\text{0}$$
(30)

In contrast,${\text{ CV}}_{\text{stride}-\text{time}}$, a dimensionless ratio-based variable that may have a skewed distribution, change will be computed using the natural log-ratio of cue value to baseline:

$$\Delta_{log}=\text{log}\left(\text{Cue Value}+\in \right)-\text{log}\left(\text{Baseline Value}+\in \right)$$
(31)

where 𝜖 is a small constant to avoid the logarithm of zero. This transformation was chosen as ${\text{CV}}_{\text{stride}-\text{time}}$ is a ratio-based measure that can be highly skewed and exhibit unequal variances across conditions. Applying the *log* transformation to change scores helps to normalise the distribution and stabilise the variance, thereby supporting more reliable statistical comparisons of cueing effects on ${\text{CV}}_{\text{stride}-\text{time}}$ in this within-subjects design. Post-hoc comparisons between cueing modalities will be conducted using paired t-tests, with Bonferroni correction applied to account for multiple comparisons. Effect sizes will be reported using Cohen’s d.

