If assumptions for normality are not met, a Friedman test will be used to assess within-subject differences across cueing conditions. Post-hoc Wilcoxon signed-rank tests, with Bonferroni correction, will be conducted only if the Friedman test is statistically significant. For between-subject effects (e.g., walk order), where normality assumptions are violated, the Kruskal–Wallis test will be used to assess group-level differences between walk-order groups. Interaction effects between cueing and walk order will be explored non-parametrically by conducting separate Friedman tests within each walk order group. Effect sizes for non-parametric tests will be calculated using the rank-biserial correlation coefficient, $\text{r}=\text{Z}/\sqrt{\text{N}}$, providing a measure of the magnitude of the effects observed.

For the three primary comparisons, we will control the familywise error rate using a Bonferroni adjustment. Given three cueing modalities, statistical significance (*p*) will be evaluated at a two-sided α = 0.01/3 = 0.0033. Effect sizes (i.e., SRM) and 95% confidence intervals will also be reported. Secondary and exploratory analyses (e.g., comparing cueing modalities to one another, examining washout effects, assessing stride-to-stride variability) will not be subject to multiplicity correction. For these analyses, a two-sided *p*-value of 0.05 will be considered statistically significant across all parametric and nonparametric tests.

To assess whether the first cue produced short-term residual effects, we will calculate changes in gait outcomes from baseline to each cued walk and from each cued walk to its subsequent washout walk (WO1 and WO2). For each cue exposure, a carryover score will be calculated as the difference between the change induced by the cue and the change observed during the corresponding washout period, reflecting retained cue effects. The approach enables an evaluation of carryover effects after each cued walk separately, thereby capturing any cumulative or progressive retention of cueing effects. Group differences based on initial cue type (i.e., counterbalanced sequence) will be evaluated using one-way ANOVA or the Kruskal–Wallis test, depending on normality assumptions [74–80].

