### Primary objectives: Validity and evaluating the effects of personalised auditory cues on gait

The impact each personalised auditory cue has on participants’ stride length, gait speed, and${\text{ CV}}_{\text{stride}-\text{time}}$ are a significant exploratory interest. These metrics, in particular${\text{ CV}}_{\text{stride}-\text{time}}$, where a decrease is known to reduce the risk of falling, have indicated variable effects among PwPD in other cueing-related studies, particularly where music cueing is not personalised [9,44,73]. The findings from this study will establish a baseline understanding of their (i) validity (from an app and smartphone worn on the lower back) and (ii) whether personalised cues can consistently reduce stride variability across a broader range of participants.

Observed gait responses will be interpreted in the context of sequence-conditional effects (cue order, exposure, and adaptation over time), and not as definitive evidence of causal superiority of one cueing condition over another. Analyses of gait variability and asymmetry will be interpreted cautiously, as these measures typically exhibit greater dispersion and may be underpowered (as sample size of based on gait speed). Emphasis will be placed on estimating effect sizes and examining consistency of responses across conditions, rather than on formal hypothesis testing.

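### The walk-order main effect cannot detect walk-position effects (practice, fatigue, adaptation); they fall inside the cue-by-walk-order interaction, and no planned test isolates them

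*Protocol article*

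**What the plan says.** The main model is described thus: "A two-way mixed ANOVA will be used to assesses the effects of cueing modality and walk order on outcomes". In it, "cueing modality will be modelled as a within-subject factor, while walk order as a between-subject factor to account for potential sequence effects". If normality fails, "the Kruskal–Wallis test will be used to assess group-level differences between walk-order groups", and the interaction of cue and walk order is explored by a separate Friedman test in each group (Statistical analysis).

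The three sequences of 20 participants each, listed under Walking/gait tasks, are:
- Sequence 1: "NC, Me, WO1, IM, WO2, and VM"
- Sequence 2: "NC, IM, WO1, VM, WO2, and Me"
- Sequence 3: "NC, VM, WO1, Me, WO2, and IM"

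The Discussion, under Primary objectives, says that gait responses will be interpreted in the context of "sequence-conditional effects (cue order, exposure, and adaptation over time"). No term for position in the session (Walk #2, #4 or #6) appears in any described analysis.

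**The concern.** The walk-order factor is the plan's stated means of accounting for sequence effects. In a cyclic design, however, a comparison of sequence groups asks whether the groups have the same average change over the three cues. It does not ask whether the first, second and third cued walks differ. Practice, fatigue and adaptation act through position, and every group passes through all positions.

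The risk is one of interpretation. A non-significant walk-order main effect could be taken as reassurance about practice or fatigue when it carries no information on either. A real position effect would surface under another label: as cue effects that vary by sequence in the ANOVA, or as a cue effect within a group in the rank route. The Discussion commits to interpreting adaptation over time, and no planned test separates it.

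**Working it through.** **1. Where a position effect goes.** Reading position off the three sequences:

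| | Me | IM | VM |
|---|---|---|---|
| Sequence 1 | 1 | 2 | 3 |
| Sequence 2 | 3 | 1 | 2 |
| Sequence 3 | 2 | 3 | 1 |

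Let position p add τ_p, the same for all cues. Each row mean is (τ1+τ2+τ3)/3, and so is each column mean. The sums of squares for sequence and for cue are therefore both 0, and everything lies in cue × sequence. For τ = (0, 1, 2), the sums over the nine cells are sequence 0, cue 0, interaction 6, total 6. No variance assumption is involved.

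**2. Power of the available tests.** The article gives no drift size and no variance for cue-to-cue differences, so these are assumptions: linear drift, SD of a cue-to-cue difference = 1 (within-person error variance 0.5 per walk), 20 per sequence, α = 0.05. For a drift of s SD per walk, six of the nine cells are shifted by ±s, and the noncentrality is λ = 20 × 6s² / 0.5 = 240s². That gives λ = 3.75, 15 and 60 at s = 0.125, 0.25 and 0.5.

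| Drift per walk | Sequence main effect | Kruskal–Wallis | Cue × sequence (4 df) | Position term (2 df) |
|---|---|---|---|---|
| 0 | 0.05 | 0.05 | 0.04 | 0.05 |
| 0.125 | 0.05 | 0.04 | 0.31 | 0.40 |
| 0.25 | 0.05 | 0.05 | 0.88 | 0.94 |
| 0.5 | 0.05 | 0.05 | 1.00 | 1.00 |

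These are rejection rates from 2,000 simulated trials per row. The noncentral F distribution with the λ above agrees to within about 0.02 for the last two columns. Kruskal–Wallis was applied to each participant's average over the three cues.

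**3. Rank route.** Within one sequence group each cue always occupies the same position, so a Friedman test cannot tell cue from position. With no cue effect:
- No drift: the chance of at least one significant test among three is 1 − 0.95³ = 0.14 (simulated 0.14 to 0.16).
- Drift 0.25 per walk: each test rejects about 0.36 of the time, so 1 − 0.64³ = 0.74 (simulated about 0.75).

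**4. Cue-versus-cue paired t-tests.** Between any two cues, the position difference over the three sequences is +1, −2, +1 in some order. Its mean is 0, so there is no bias. Its variance is (1 + 4 + 1)/3 = 2, so the variance of the paired differences rises from 1 to 1 + 2s², which is 1.125 at s = 0.25 and 1.5 at s = 0.5. For a 0.5 SD cue difference with n = 60 and two-sided α = 0.05/3 (critical t about 2.46), power ≈ Φ(0.5√60 − 2.46√(1 + 2s²)), where 0.5√60 = 3.87:
- s = 0: Φ(1.41), about 92%
- s = 0.25: Φ(1.26), about 90%
- s = 0.5: Φ(0.86), about 80%

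Simulation gives about 91–92%, 88–90% and 78–81%. Without Bonferroni, at 0.05, the figures are about 97%, 96% and 92%. Both levels are shown because the section applies Bonferroni to the post-hoc paired tests in one place and exempts cue-to-cue comparisons from correction in another. With position in the model, power at 0.05/3 is about 92–93% whatever the drift.

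**The case against.** A reader might infer three stronger things, and the documents support none of them.

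- **Walk order is tested only between groups.** A two-way mixed ANOVA carries the cue-by-walk-order interaction, and the article names that interaction when it describes the rank alternative.
- **A real order effect would be reported as absent.** The interaction absorbs the whole position effect. At 0.25 SD per walk it gives up only about 6 points of power to a dedicated position term (0.88 against 0.94), and at 0.5 nothing. The very large gap of 0.05 against 0.94 applies to the main effect alone. The likelier failure is a wrong label, not a missed signal.
- **The comparison of cues is biased.** With balanced, complete data it is not. The omnibus cue test in the mixed ANOVA is also unaffected, because the interaction is removed from the error term.

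It can further be said that the article nowhere states that a null walk-order effect will be read as absence of practice or fatigue. It puts estimation ahead of formal testing, and the uncued washout walks give some information on change over the session. A position term also only re-expresses 2 of the 4 interaction df. All of this stands, and it limits the weight of the point. It does not answer it: the factor offered to account for sequence effects cannot respond to position, the interaction is not described as the place to look for it, and the Friedman tests within groups cannot separate position from cue.

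**Conclusion.** The point holds in limited form. The walk-order main effect has no power beyond α against an additive position effect. That follows from the sequences themselves and needs only that each participant completes all three cued walks. That the effect also drops out of the cue main effect requires equal group sizes as well. For Kruskal–Wallis, the conclusion assumes that the test is the rank counterpart of the main effect, on each participant's average over cues; the article does not say.

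The consequences are moderate. There is a risk of misreading the interaction, a rank route in which drift imitates a cue effect (about 75% chance of at least one significant Friedman test at 0.25 SD per walk, against about 15% without drift), and a loss of precision in the paired t-tests that is slight at 0.25 SD per walk and about 12 points at 0.5. These sizes rest on the assumed linear drift and variances. A drift of 0.5 per walk is a full SD between first and third cued walk and should be seen as the upper end.

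**What to change.** Add walk position (#2, #4, #6) as a within-subject term beside cue, for example a linear mixed model with participant, cue, position and, optionally, sequence. Use the position term as the test of order, and take cue-versus-cue contrasts from that model. Do not present the sequence main effect, the Kruskal–Wallis test or the Friedman tests within groups as tests of position.

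State one limit alongside this. Baseline is always Walk #1, so every cue-versus-baseline change, which is the primary comparison, still carries the average drift of the later walks. Modelling position among the three cued walks does not remove it.

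The cost is wording in the analysis section and 2 of about 118 within-subject df (60 × 2 = 120, less 2 for cue). Position follows from the allocated sequence, so no new data and no design change are needed.

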#### Walking/gait tasks.

Participants will choose from a selection of music tracks that span genres including pop, rock, R&B, and country. All walks will be 1-minute in duration in a continuous 25m loop, including two 8.5m straight segments and two 4m turns, Fig 3. Walk #1 will be at the participant’s natural walking pace to calculate a baseline cadence, i.e., a walk with no cueing (NC). Walks #2, #4, and #6 will be cued, with external auditory stimuli (BPM set at +10% of baseline cadence) which are metronome (Me), instrumental music (IM), and vocal music (VM). Participants will be assigned to one of three counterbalanced cue sequences for Walks #2, #4, and #6. For example, the first participant enrolled to the study follows Sequence 1, the second follows Sequence 2, the third follows Sequence 3, and the fourth cycles back to Sequence 1, etc.

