#### Sample size.

Sample size calculations were based on detecting changes in gait speed using a within-subject design. Assuming a standardised response mean (SRM) of 0.5 (moderate effect size) for gait speed, a two-sided significance level (α) of 0.01, and 90% power, approximately 54 participants would be required to detect a statistically significant change in gait speed for a single comparison (e.g., cued vs. non-cued walking). When accounting for the three cueing conditions and the associated adjustment for multiple (three) comparisons, we applied a Bonferroni correction resulting in an adjusted alpha of α (0.01/3 = 0.0033). That requirement increases sample size to approx. 55 participants. However, to allow for an anticipated attrition rate of up to 10%, we plan to recruit 60 participants in total. This sample size ensures adequate power to detect moderate cueing effects on gait speed, accommodates potential dropouts, and provides balanced representation across randomisation sequences.

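### The three primary comparisons are each cue against uncued walking, but every cue-effect test the plan names compares the cues with each other, and the uncued walk is never rotated

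*Protocol article*

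**What the plan says.** The Sample size section assumes SRM 0.5 for gait speed, with "a two-sided significance level (α) of 0.01, and 90% power", and states the number needed "to detect a statistically significant change in gait speed for a single comparison (e.g., cued vs. non-cued walking"). It then divides alpha by three for the three cueing conditions. The Statistical analysis section repeats 0.01/3 = 0.0033 for three primary comparisons. It puts comparison of the modalities with one another among the secondary and exploratory analyses, at 0.05.

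The same section describes the tests. Outcomes are expressed as change: "within-participant changes from baseline will be calculated using cue-specific difference scores". A two-way mixed ANOVA takes cueing modality within subjects and walk order between subjects. Post-hoc paired t-tests are between modalities. If normality fails, "a Friedman test will be used to assess within-subject differences across cueing conditions", and Wilcoxon tests follow only if Friedman is significant. SRMs and 95% confidence intervals are also to be reported.

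Under Walking/gait tasks, Walk 1 serves "to calculate a baseline cadence, i.e., a walk with no cueing (NC"), and it comes first in all three sequences. The cues occupy Walks 2, 4 and 6. The uncued Walks 3 and 5 are the washout walks, meant "to further reset their gait but also to assess whether any carryover effect remains before the next cue begins". In the analysis they enter only the carryover assessment.

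**The concern.** There are two linked problems.

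First, the question the trial is sized for and the questions its tests answer differ. Once Walk 1 has been subtracted, uncued walking is no longer a level of any factor. The modality effect asks whether the three mean changes differ from each other, not whether any of them differs from zero. The second primary objective, the effect of the cues on gait, therefore has an alpha but no stated test.

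Second, when that test is supplied, its natural comparator is Walk 1. The three sequences balance the cues against each other but never move the uncued walk, so anything that changes between Walk 1 and the later walks is counted in every cue's change score.

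**Working it through.** **Which comparisons are primary.** Sample size names cued versus non-cued walking, and cue-versus-cue is explicitly secondary. Three cues against one uncued reference give three comparisons, which matches 0.01/3.

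**What each named test examines.** Let the mean change from Walk 1 be δ(Me), δ(IM) and δ(VM).
- ANOVA modality effect and Friedman: δ(Me) = δ(IM) = δ(VM).
- Paired t or Wilcoxon follow-up: differences between pairs of δ.
- Walk order: whether the average change differs between sequences.
- None is stated to test δ = 0.

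If all three δ are equal, the modality null is true whatever their common size. Simulation check (2,000 runs, 54 completers, the documented sequences, true SRM 0.5 for every cue, tests at 0.05): ANOVA rejects in 5.4% and Friedman in 5.4%. A test of one cue against Walk 1 at 0.0033 rejects in about 70%.

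**The plan's own figure.** The stated 54 (alpha 0.01) and 55 (alpha 0.0033) do not reproduce for a paired test. With n = ((z for alpha + z for power)/SRM)², two-sided 0.01 and 90% power give 60 (63 by exact t), and 0.0033 gives 72 (76 by exact t). Exact t power at 0.0033 is 72% with 54 completers and 79% with 60. This is a separate matter, but it is the power of the test proposed below.

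**Intervals.** Alpha 0.0033 corresponds to a 99.67% interval. With 54 completers a 95% interval excludes zero when the observed SRM exceeds 2.006/√54 = 0.27. The 0.0033 rule needs 3.074/√54 = 0.42. The 95% intervals therefore cannot stand in for the primary decision.

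**Walk 1 as sole comparator.** The documents give no drift size, so these are assumptions, in SD-of-change units. With no cue effect and a constant shift after Walk 1, a test of one cue against Walk 1 at 0.0033 with 54 completers rejects with these probabilities:

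| Assumed shift | Rejection |
|---|---|
| 0.1 | 1.3% |
| 0.2 | 6.4% |
| 0.3 | 20.6% |
| 0.4 | 45.4% |

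A shift toward worse gait would instead hide a real benefit.

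**What a six-walk model can and cannot do.** Fit condition, linear walk number (w = 1 to 6) and participant. The sequences are balanced, so the three cue contrasts coincide with the coefficient of a cued indicator c = (0,1,0,1,0,1). Sums of squares and products: Sww = 17.5, Scc = 1.5, Scw = 1.5. The coefficient is (Sww·Scy − Scw·Swy)/(Sww·Scc − Scw²), with denominator 26.25 − 2.25 = 24.
- Pure step after Walk 1, y = (0,1,1,1,1,1): Scy = 0.5, Swy = 2.5. Coefficient = (8.75 − 3.75)/24 = 0.208, so about 21% of the step remains as apparent cue effect, against 100% with Walk 1 alone.
- Cue effect 1 with 30% retained in Walks 3 and 5, y = (0,1,0.3,1,0.3,1): Scy = 1.2, Swy = 1.8. Coefficient = (21 − 2.7)/24 = 0.7625, so about 76% of the effect is recovered.

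**The case against.** The strongest reply is that only the name of a test is missing. The comparison, the alpha and the change score are all fixed, a paired or one-sample test on that change is the obvious reading, and an article may leave the name to a fuller plan. This has some force, and it is why one added sentence largely repairs the first problem. It does not remove the point: the section is a test-by-test plan with fallbacks, post-hoc tests and alphas, and all the cue-effect tests it names answer the question it calls secondary. The ANOVA intercept on change scores would test the average over cues, but the text does not name it, and it is not three comparisons.

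A reader might infer that the plan would report no effect if all cues helped equally. The documents do not support that: the promised SRMs and intervals would show a common benefit.

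On drift, the plan is not blind. It computes the change from a cued walk to the following washout walk, though Walk 6 has none. Progressive drift over Walks 2, 4 and 6 would appear in the modality-by-order interaction. The Discussion says responses will be read in light of cue order, exposure and adaptation, with emphasis on effect sizes. These points stand. But a shift between Walk 1 and all later walks, common to every sequence, cancels from modality, order and their interaction alike. The Discussion's caution disclaims superiority between cues and alters no estimate.

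It is also fair that the walks last one minute with seated breaks, and that no source supports any particular drift.

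**Conclusion.** The concern holds in this form: as written, the primary cue-versus-uncued comparisons have an alpha but no named test, and the tests that are named would reject only at their nominal level under an equal benefit from all cues. This rests on the text alone.

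The second part is a design limit that the analysis can only partly address. Change from Walk 1 cannot separate a cue effect from a shift common to all later walks. Its direction and size are unknown. The rejection rates of 6% to 45% for shifts of 0.2 to 0.4 are illustrations. It would be wrong to read them as this trial's error rate, since they assume the drift and presuppose a Walk 1 test that the plan does not name.

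Nor should a reader conclude that the six-walk model must replace the Walk 1 comparison or that it raises power. Its smaller contrast variance (0.0233 against 0.0333 σ² with 60 participants) assumes equal residual variances and no carryover into washout walks, and the protocol records those walks partly because carryover is in doubt.

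**What to change.** 1. Name the three primary tests: metronome, instrumental music and vocal music, each against uncued gait speed. For example, use a one-sample or paired t-test of the change from Walk 1 (Wilcoxon signed-rank if non-normal) at two-sided 0.0033. State that they are not gated by the ANOVA or Friedman result, and give intervals matched to that alpha (99.67%). Label the ANOVA, Friedman and post-hoc cue-versus-cue tests as secondary.
2. Prespecify, beside the primary result, a mixed model on all six walks: condition (uncued, Me, IM, VM) and walk number as fixed effects, participant as random effect, with Walks 3 and 5 as further uncued comparators. If it and the Walk 1 result disagree, limit the cue-versus-uncued conclusion accordingly.
3. State as a limitation that the uncued walk is never rotated.

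The cost is analysis wording only, since all six walks are already recorded. The change should be dated and made before outcomes are examined, or else be reported as post hoc. The downside is that carryover into Walks 3 and 5 pulls the six-walk estimate toward zero, and its linear term removes only part of a single step after Walk 1. No power gain should be claimed for it.

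### On the rank route, the cue-by-walk-order interaction is examined by separate Friedman tests in each sequence group, which do not test interaction and can give split verdicts from a plain cue effect.

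*Protocol article*

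**What the plan says.** The parametric plan in the Statistical analysis section is a two-way mixed ANOVA in which "cueing modality will be modelled as a within-subject factor, while walk order as a between-subject factor to account for potential sequence effects". Walk order is therefore the sequence group, and this model contains a proper cue-by-order term.

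If normality is not met, the same section moves to rank tests. For the cue main effect, "a Friedman test will be used to assess within-subject differences across cueing conditions". For the main effect of walk order it names the Kruskal–Wallis test on overall group differences. For the interaction, "Interaction effects between cueing and walk order will be explored non-parametrically by conducting separate Friedman tests within each walk order group". It names no comparison of the three groups' cue patterns, and no rule for turning three p-values into a statement about interaction.

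On the design, the Walking/gait tasks section states that "Participants will be assigned to one of three counterbalanced cue sequences for Walks #2, #4, and #6". The first is given as "Sequence 1–20 participants: NC, Me, WO1, IM, WO2, and VM" and the second as "Sequence 2–20 participants: NC, IM, WO1, VM, WO2, and Me". The third continues the rotation (VM, Me, IM).

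Secondary and exploratory analyses "will not be subject to multiplicity correction", and for them a p-"value of 0.05 will be considered statistically significant across all parametric and nonparametric tests".

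**The concern.** The null hypothesis of no interaction is that the cue pattern is the same in every sequence group. The null hypothesis of a Friedman test within one group is that the three cued walks do not differ in that group. The second is false whenever the cues truly differ, even if they differ identically everywhere. The article uses the Friedman test for the cue main effect, and running it three times in subgroups does not change what it tests.

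The practical risk is a split verdict. With 20 people per group and moderate power, one or two groups will often reach significance and the rest will not, through chance alone. Three p-values with no stated rule invite the reading that the cue effect depends on order. The Discussion says gait responses will be interpreted in the light of sequence-conditional effects, and on the rank route this is the only analysis of whether cue effects differ by order. The route is plausible: Shapiro–Wilk tests are planned on residuals and within each cue condition, and the article itself expects that stride-time CV may be skewed.

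**Working it through.** The article gives no power or error rate for the interaction analysis, so there is no stated figure to reproduce.

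**Inputs from the article:** three cyclic sequences of 20; level 0.05 with no correction. At 10% attrition, 60 × 0.9 / 3 = 18 per group.

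**Assumption:** the SRM of 0.5 in the Sample size section is for cued versus non-cued walking, and no cue-versus-cue effect is given. The main runs place both music cues 0.25 or 0.5 SD above the metronome in every group, where SD is that of a within-person cue-cue difference.

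**Step 1: formula.** The groups are independent. If each Friedman test rejects with probability p:
- P(at least one rejects) = 1 − (1 − p)³
- P(split, one or two of three reject) = 1 − (1 − p)³ − p³ = 3p(1 − p), which peaks at 75% when p = 0.5.

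With no effect at all, p = 0.05 gives 1 − 0.95³ = 14.3% for at least one rejection.

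**Step 2: plain cue effect, no interaction, by simulation.**

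| Cue effect | At least one group rejects | Groups split | Direct between-group test |
|---|---|---|---|
| 0.25 SD, 20 per group | about 40% | about 40% | about 4–5% |
| 0.5 SD, 20 per group | 86% | 75–76% | about 4–5% |
| 0.5 SD, 18 per group | 79% | 72% | not run |

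Check at 0.5 SD: each test rejects in 47%, so 1 − 0.53³ = 85% and 3 × 0.47 × 0.53 = 75%. Check at 0.25 SD: at least one rejection in 40% implies p = 1 − 0.60^(1/3) = 0.157, and 3 × 0.157 × 0.843 = 40%. The formula and the simulation agree within simulation error.

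**Step 3: sensitivity.** A second set of runs used equally spaced cues, with a best-minus-worst range of 0.3 / 0.5 / 0.8 / 1.0 within-subject error SD. This scale differs from step 2: the SD of a difference is √2 times the error SD.
- Normal errors: at least one group rejects in 28 / 51 / 84 / 96%, and the groups split in 28 / 50 / 75 / 70%.
- Heavy-tailed t(3) errors: 39 / 73 / 98 / 100%, and 39 / 69 / 59 / 31%.
- Direct tests (mixed-ANOVA interaction, or Kruskal–Wallis on within-person contrasts): 3.5–5.5% throughout.

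Splits become rarer once power is high enough for all three groups to reject.

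**Step 4: walk position.** Everyone in a group has the same order, so cue and position are fully aliased within it. Across groups, take a trend of 0.25 SD per walk and no cue effect. IM − Me is then +0.25 in Sequence 1 (walks 2 and 1), −0.50 in Sequence 2 (walks 1 and 3) and +0.25 in Sequence 3 (walks 3 and 2). The cue difference really does vary by sequence, so under the plan's definition of walk order this is an interaction. It occupies 2 of the (3 − 1)(3 − 1) = 4 degrees of freedom. In simulation of this trend the mixed-ANOVA interaction term rejects in 88%, Kruskal–Wallis on contrasts in about 74%, and at least one Friedman test in 73–75%. A cue-by-sequence test with position removed first (2 df) stays at 3.6–5.6% in the step 3 runs under a cue effect, a position trend, or both.

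**The case against.** Four points deserve weight.

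1. The step is worded as exploration and has no decision rule, so a split verdict counts as false interaction only if the analyst reads it that way. This stands. A reader might infer that a false interaction will be reported; the text supports only that one could be.

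2. The branch applies only if normality fails. The main analysis has a valid interaction term, and stride-time CV is log-transformed in advance. The interaction is not among the three primary comparisons, and the Discussion puts effect sizes ahead of formal testing. This stands, and it limits the severity.

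3. A reader might infer that rejection caused by a position trend is also a false interaction. The article does not support that. It defines walk order as the sequence group, and with cyclic sequences a position trend is a cue-by-sequence interaction in that model. The mixed ANOVA would flag it as well. What remains is that the within-group tests cannot tell cue from position.

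4. The effect size is the reviewer's assumption, and the split rate falls to about 40% at 0.25 SD. This stands, which is why a range is shown.

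None of this makes a within-group Friedman test a test of interaction. Nor can the gap be put down to detail left for a fuller document, because the article names the method. The Kruskal–Wallis test on overall group differences and the carryover scores answer other questions.

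**Conclusion.** The point holds in a limited form. The named rank procedure does not test the cue-by-walk-order interaction. Under a cue effect common to all groups, it gives at least one significant group in about 40% to 86% of trials and a split verdict in about 40% to 76%, where a direct test would reject in about 4–5%. These figures assume a cue effect of 0.25 to 0.5 SD of a cue-cue difference, normal errors, 20 per group and tests at 0.05. The mismatch of null hypotheses needs none of those assumptions. Severity is minor to moderate: the method is wrong for its stated purpose, but it sits in an exploratory branch used only when normality fails.

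**What to change.** Replace the separate Friedman tests with a direct between-group test of within-person cue contrasts that includes walk position. Examples are an aligned-rank or rank-transformed cue-by-sequence test, or a mixed model, with position fitted first and the remaining 2 df tested as the interaction. State that without the position term a position trend will also be flagged: Kruskal–Wallis on the contrasts alone, for instance, rejects in about 74% at 0.25 SD per walk. Report within-group cue patterns descriptively, noting that cue and position cannot be separated within a group.

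The cost is one or two sentences of analysis wording and no new data. The interaction test drops from 4 to 2 degrees of freedom, so it addresses only departures beyond cue and position effects.
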